### Participant eligibility

#### Inclusion criteria

Women who meet the following criteria will be eligible to participate in the study: (1) 18–60 years of age; (2) diagnosed with stage I-III (i.e., non-metastatic) breast cancer; (3) scheduled to receive at least six cycles of adjuvant or neoadjuvant chemotherapy; (4) can speak and comprehend English (in order to perform neuropsychological test battery) and; (5) have support from their medical oncologist to participate in the yoga intervention. They must also score ≥23 on the Montreal Cognitive Assessment (MoCA) (42) and ≥ 55 on the LVEF of echocardiography before randomization.

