### Data collection

#### Assessment of cognitive functioning

Participants complete a neuropsychological test battery at four of the five study time points [baseline (pre-intervention), end of chemotherapy (post-intervention/primary endpoint), 16 weeks post-chemotherapy (first follow-up), and one-year post-baseline (second follow-up)]. The battery covered attention/working memory, verbal and visual memory, executive functioning, planning and processing speed. These cognitive domains were chosen because previous studies have shown that they are sensitive to the deleterious effects of chemotherapy (46). The tests are performed in the following order: Colour Trials Test conditions 1&2 (attention), Digit Span Test (Memory and Recall), Stroop Test (Executive functioning), Digit-Symbol Substitution Task (processing speed), Rey auditory Verbal Learning Test (Verbal Learning and memory), Tower of London (planning and executive functioning), and Visual Reproduction task (visual learning and memory). To minimize the effects of practice, different testing forms are used at different time points. The scheme of Neuropsychological test battery planned to use in the study is depicted in **Table 2**.

**Table 2 T2:** Neuropsychological test battery.

Domain	Functions	Test	Source	Time Taken
Speed	Mental Speed	Digit Symbol Substitution	NIMHANS Neuropsychology Battery	5-7 minutes
Attention	Focussed Attention and Cognitive Flexibility	Colour Trails Test 1 & 2	NIMHANS Neuropsychology Battery	8-10 minutes
Executive Function/ Language	Phonemic Fluency	Controlled Oral Word Association Test	NIMHANS Neuropsychology Battery	5 minutes
	Semantic Fluency	Animals Names Test	NIMHANS Neuropsychology Battery	3 minutes
Executive Functions	Verbal Working Memory	Verbal N Back Test (1 back and 2 Back)	NIMHANS Neuropsychology Battery	5-7 minutes
	Response Inhibition	Stroop Test	NIMHANS Neuropsychology Battery	10-12 minutes
Visuo-Spatial	Visuo-Spatial Construction	Rey Complex Figure Test	NIMHANS Neuropsychology Battery	10-15 minutes
Learning and Memory	Visual Memory	Rey Complex Figure Test		
	Verbal Memory	Rey Auditory Verbal Learning Test	NIMHANS Neuropsychology Battery	15 minutes
Language	Speed Reading	Comprehension

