##### Serum brain-derived neurotrophic factor (BDNF)

Assessment takes place at four out of five-time points: baseline, end of chemotherapy, first follow-up, and second follow-up. 5 ml of whole blood will be collected in a heparinized tube using a vacutainer system at each time point. Then samples will be immediately centrifuged at 2500 rpm for 10-15 min. The serum will be stored at −80°C until analysis. The serum BDNF level will be quantified using an enzyme-linked immunosorbent assay (ab212166, Abcam, Cambridge, UK).

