##### Statistical analyses

Data will be analyzed using IBM SPSS (Version 22.0 for Windows). Sociodemographic and medical characteristics will be characterized using descriptive statistics. To evaluate attrition bias, sociodemographic and medical factors at baseline will be compared between participants who completed all assessments and those who dropped out. Under the “missing at random” assumption, characteristics usually linked with attrition (e.g., age, chemotherapy duration) will be included as covariates in all analyses.

The data will be analysed for intention to treat analysis accounting for dropouts in the groups. Data will be analysed at baseline (before chemotherapy starts), after three and six cycles of chemotherapy. We will; also try to analyse six months and one-year follow-ups. A repeated measures ANOVA will be done using *post hoc* Bonferroni correction. A p-value ≤ 0.008 will be considered significant (95% confidence interval) for a 2 group assignment over three-time points (interaction effects). Secondary analyses will be carried out to determine the bivariate relationships between predictor and outcome variables. Further regression analyses will be done to understand the mediation and moderation effects if any.

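### The planned three-time-point analysis cannot be run on the neuropsychological battery, BDNF or cortisol, which are not measured mid-chemotherapy, and two of its time labels do not match the visit schedule

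*Protocol article*

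**What the plan says.** **Analysis.** The protocol article, Statistical analyses, sets the times: "Data will be analysed at baseline (before chemotherapy starts), after three and six cycles of chemotherapy". The method is repeated measures ANOVA, with this rule: "A p-value ≤ 0.008 will be considered significant (95% confidence interval) for a 2 group assignment over three-time points (interaction effects". It then adds: "We will; also try to analyse six months and one-year follow-ups". No outcome is exempted.

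**Visits.** Study design has five assessments: baseline, midway through chemotherapy, after chemotherapy, 16 weeks after chemotherapy and one year after baseline.

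**Battery.** Assessment of cognitive functioning states: "Participants complete a neuropsychological test battery at four of the five study time points". After baseline it lists "end of chemotherapy (post-intervention/primary endpoint), 16 weeks post-chemotherapy (first follow-up" and the one-year visit. The visit left out is the mid-chemotherapy one. The Abstract places this battery among the primary objectives.

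**Blood markers.** For BDNF: "Assessment takes place at four out of five-time points: baseline, end of chemotherapy, first follow-up, and second follow-up". The Serum cortisol section gives the same four visits.

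**Course length.** Inclusion criteria require patients "scheduled to receive at least six cycles of adjuvant or neoadjuvant chemotherapy". The Integrated Yoga Therapy program section speaks of six cycles at 21-day intervals, of an intervention of 14 to 24 weeks that runs until chemotherapy ends, and (below Table 1) of 18 weeks.

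**A second analysis.** Sample size estimation names ANCOVA with the baseline value as covariate, and two-tailed p < 0.05.

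**The concern.** The analysis section and the data collection sections describe different sets of time points. A group-by-time test over three times needs values at all three. Where the middle visit is omitted by design, its value is absent for every patient, so this is not a missing-data problem that a missing-at-random assumption could repair.

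One of the affected outcomes is a primary objective. As written, the analyst must improvise a method, a threshold and possibly a time point for it once data are in hand. Those choices should be fixed beforehand. The two loose labels, six months and six cycles, leave further room to choose.

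**Working it through.** **Step 1. Match measured visits to the three analysis times.** I read after three cycles as the mid-chemotherapy visit and after six cycles as the post-chemotherapy visit, which is the most favourable reading for the plan.

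| Outcome | Baseline | Mid | End | Times available |
|---|---|---|---|---|
| EORTC QLQ-C30 | yes | yes | yes | 3 of 3 |
| Perceived stress scale | yes | yes | yes | 3 of 3 |
| Ryff well-being | yes | yes | yes | 3 of 3 |
| Neuropsychological battery | yes | no | yes | 2 of 3 |
| BDNF | yes | no | yes | 2 of 3 |
| Cortisol | yes | no | yes | 2 of 3 |

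The EORTC and Ryff sections list baseline and pre-chemotherapy separately while counting five times. Study design treats these two as one visit, and so do I. HRV and echocardiography are left out because the text gives no visit schedule for them and the schedule figure is not shown.

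**Step 2. The threshold.** 0.05 / 6 = 0.0083, which agrees with the stated 0.008. The article does not say where six comes from; 2 groups × 3 times = 6 is the obvious reading, and the rule itself refers to three times. It has no clear meaning for an outcome with two.

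**Step 3. The six-month label.** One month is 365.25 / 12 / 7 = 4.35 weeks, so six months is 26.1 weeks.
- Counted from the end of chemotherapy, the first follow-up is at 16 weeks: 16 / 4.35 = 3.7 months.
- Counted from the start, assuming chemotherapy lasts as long as the intervention: 14 + 16 = 30 weeks (6.9 months), 18 + 16 = 34 weeks (7.8 months), 24 + 16 = 40 weeks (9.2 months).
- Yoga may start up to a week before chemotherapy. Taking that week off the shortest course gives 13 + 16 = 29 weeks (6.7 months).
- For the first follow-up to fall at six months from the start, chemotherapy would have to last 26.1 − 16 = 10.1 weeks, which is shorter than any stated duration.

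The one-year visit falls 6.5 to 8.8 months after chemotherapy for courses of 24 to 14 weeks, but the plan lists one year separately.

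**Step 4. Six cycles against end of chemotherapy.** 6 × 21 / 7 = 18 weeks, which reproduces the stated 18. The stated 14 to 24 weeks would be 14 / 3 = 4.7 to 24 / 3 = 8.0 cycles of 21 days. The lower figure conflicts with a minimum of six cycles and the upper with exactly six. The sections therefore disagree on cycles and duration. Since eligibility sets only a minimum, the end of six cycles need not be the end of chemotherapy, and three cycles need not be midway. The analysis section itself lists chemotherapy duration as a covariate, so some variation is expected.

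**The case against.** **The powered outcome is unaffected.** Sample size estimation rests on the EORTC cognitive domain, which is measured before, during and after chemotherapy. This stands. A reader might infer that the trial's main outcome cannot be analysed as planned, and the article does not support that. The battery is one of the other primary objectives; BDNF and cortisol are secondary.

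**A workable method is already named.** The ANCOVA under Sample size estimation needs only baseline and one later value, which all three affected measures have. This also stands, and it makes the remedy easy. It does not remove the problem, because Statistical analyses prescribes something else for every outcome and does not say which method governs.

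**Six months is a label slip.** Two follow-ups are named for analysis and two are scheduled, so the first most likely means the 16-week visit. It would go too far to say that this analysis would have no data. What stands is that the label matches no scheduled visit.

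**A six-week gap in the endpoint is not shown.** One might read 24 weeks as eight 21-day cycles and place the end of six cycles (week 18) six weeks before the end of treatment. That conversion is an inference: it fails at 14 weeks, and the intervention section also says six cycles and 18 weeks. Nor would on-treatment and post-treatment battery scores be mixed, since visits are scheduled by treatment state and the first battery test after baseline is at the end of chemotherapy. What stands is two names for one endpoint, which can diverge for patients with more than six cycles. The article does not say how many such patients there will be.

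**Conclusion.** The concern holds in a limited form. The three-time group-by-time ANOVA at p ≤ 0.008 cannot be executed for the battery, BDNF or cortisol, each of which has two of the three times. It can be executed for EORTC QLQ-C30, perceived stress and Ryff, where only the labels are loose. Nothing is concluded for HRV or echocardiography.

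The six-month follow-up matches no scheduled visit under either time origin: the first follow-up is 3.7 months after chemotherapy ends, or about 6.7 to 9.2 months after it starts if chemotherapy lasts about as long as the intervention. The endpoint has two definitions that coincide only for patients with exactly six cycles.

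The severity is moderate. A stated analysis fails for one primary objective and two secondary outcomes, but the powered outcome can be analysed and no data need be added. The first conclusion needs no assumption beyond reading the visit lists as written.

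**What to change.** In Statistical analyses:

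1. Anchor the primary comparison for every outcome to the end-of-chemotherapy assessment already named as the primary endpoint in the battery section, whatever the number of cycles, and drop the cycle-count label.
2. For the battery, BDNF and cortisol, use the baseline-adjusted ANCOVA from Sample size estimation at that visit. State a significance threshold based on the comparisons actually made, not on three time points.
3. Use the mid-chemotherapy visit only for instruments collected then.
4. Replace the six-month follow-up with 16 weeks post-chemotherapy.

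Separately, reconcile Inclusion criteria and the intervention section on the number of cycles and the duration of treatment. Which figure is right is for the investigators to say.

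The cost is wording only, with no new visits, tests or patients. The one loss is that no mid-chemotherapy inference is possible for the battery, BDNF or cortisol, and the present schedule does not allow it anyway.

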#### Sample size estimation

Considering the effect size observed, in an earlier study by Vadiraja & Rao et al. (31), with improvement in cognitive function domain of EORTC Qol-C30 between yoga and control group as 0.49 with a 95% confidence interval and 80% power, we need a sample size of 67 subjects in each arm. If attrition is within 20% through the course of the intervention, 75 subjects will be recruited in each arm. Therefore 150 consenting subjects will be randomized into each group (yoga, n=75, and controls, n=75) with an allocation ratio of 1:1. The analyses would consider a two-tailed probability of p < 0.05 as significant. This ensures that a statistical type I error (probability of detecting a false positive) is less than 5%. The analyses will involve ANCOVA using the respective baseline measure as a covariate.

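### Two competing tests and thresholds stand for the primary cognitive outcome, and the stated 80% power is established only at 0.05

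*Protocol article*

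**What the plan says.** The Abstract (Methods) makes the cognitive domain of the EORTC QLQ-C30 the primary outcome. It lists the neuropsychological battery and heart rate variability (HRV) as further primary objectives.

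Sample size estimation takes an effect from an earlier study, "improvement in cognitive function domain of EORTC Qol-C30 between yoga and control group as 0.49 with a 95% confidence interval and 80% power", and arrives at 67 per arm, with 75 per arm recruited to allow for up to 20% attrition. It then fixes a significance rule, "The analyses would consider a two-tailed probability of p < 0.05 as significant", and an analysis: "The analyses will involve ANCOVA using the respective baseline measure as a covariate".

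Statistical analyses describes something else. On timing: "Data will be analysed at baseline (before chemotherapy starts), after three and six cycles of chemotherapy". On method: "A repeated measures ANOVA will be done using" a post hoc Bonferroni correction. On the threshold: "A p-value ≤ 0.008 will be considered significant (95% confidence interval) for a 2 group assignment over three-time points", followed by a parenthesis naming interaction effects. This section does not mention ANCOVA or p<0.05. The covariates it lists as examples are age and chemotherapy duration, not the baseline outcome.

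**The concern.** One primary outcome has two tests and two significance levels, and neither section refers to the other. A p-value between 0.008 and 0.05 is a success under one rule and a failure under the other. If this is not settled before unblinding, the trial's verdict can be chosen after the data are seen.

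The power statement has the same problem. It is attached to the 0.05 rule, and no power or sample size is given for the 0.008 interaction test. Strength of the study nevertheless calls the sample size adequate without saying for which test.

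**Working it through.** **Inputs from the document.** Standardised difference d = 0.49; power 80%; two-sided 0.05; 67 evaluable and 75 recruited per arm; attrition up to 20%; 1:1 allocation (all Sample size estimation). Threshold 0.008 for the interaction over three time points (Statistical analyses).

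**Assumed, because not given.** Within-person correlation ρ (also used as the baseline correlation r) of 0.3 to 0.7, compound symmetry, and the pattern of the effect over time. No allowance is made for the attrition covariates.

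**1. Reproduce 67 per arm.** Normal approximation: n = 2(1.960 + 0.842)² / 0.49² = 2 × 7.85 / 0.2401 = 65.4, so 66. Exact two-sample t-test: non-centrality d√(n/2) = 0.49 × √33.5 = 2.84 on 132 degrees of freedom, which gives 80.4% power at n = 67. The stated figure is therefore an unadjusted t-test size at 0.05. No baseline correlation enters it; with r = 0.5, ANCOVA would need (1 − 0.25) × 66 = 49.5, about 50 per arm.

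**2. Same comparison at 0.008 (noncentral t).** Sixty per arm is 75 × 0.80.

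| n per arm | power at 0.05 | power at 0.008 |
|---|---|---|
| 60 | 75.9% | 49.7% |
| 67 | 80.4% | 55.8% |
| 75 | 84.6% | 62.3% |

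For 80% power at 0.008, the normal formula gives 2(2.652 + 0.842)² / 0.2401 = 101.7, so 102 evaluable per arm; the exact t-test needs 104.

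**3. Group-by-time interaction, 2 groups by 3 times, 67 per arm.** Non-centrality λ = (n/2) × Σ(δⱼ − δ̄)² / (1 − ρ), referred to F with 2 and 264 degrees of freedom, where δⱼ is the group difference at time j.

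- Effect growing linearly (0, 0.245, 0.49): Σ = 0.49²/2 = 0.120, so λ = 4.02/(1 − ρ).
- Full effect at both post-baseline times (0, 0.49, 0.49), or only at the last (0, 0, 0.49): Σ = 2 × 0.49²/3 = 0.160, so λ = 5.36/(1 − ρ).

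| Power at 0.008 | ρ = 0.3 | ρ = 0.5 | ρ = 0.7 |
|---|---|---|---|
| linear growth | 0.293 | 0.450 | 0.749 |
| full effect at one or both visits | 0.425 | 0.617 | 0.889 |

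**4. ANCOVA at end of chemotherapy.** The SD is multiplied by √(1 − r²); normal approximation.

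| r | n = 60, 0.05 | n = 67, 0.05 | n = 67, 0.008 |
|---|---|---|---|
| 0.3 | 0.803 | 0.844 | 0.626 |
| 0.5 | 0.873 | 0.906 | 0.733 |
| 0.7 | 0.964 | 0.978 | 0.906 |

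**5. Where 0.008 may come from.** 0.05/6 = 0.0083, and 2 groups × 3 times = 6. The document gives no derivation. Whatever its origin, one interaction test needs no six-fold correction.

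**The case against.** The conflict itself can hardly be disputed, and it is not a detail left to an analysis plan, because the article prints both rules. The stronger readings that a reader might draw from it do meet fair objections.

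- **That the 0.008 interaction decides the trial.** Neither section says so; the ANCOVA sentence is equally a statement of intent. What stands is that two rules compete.
- **That the trial was sized for ANCOVA.** ANCOVA is named, but the 67 is an unadjusted t-test size.
- **That the trial has about even odds under the 0.008 rule.** The 56% and 50% belong to an unadjusted comparison that Statistical analyses does not propose. For the interaction, the answer depends on an unstated correlation and effect pattern, and power exceeds 80% in some cases at ρ = 0.7.
- **That 0.008 counts six group-by-time cells, two of them at baseline.** This is plausible but inferred. Three pairwise time comparisons within each of two groups also make six, and the mention of post hoc correction allows that reading. The reference to interaction effects leaves it ambiguous.
- **That the 95% label is plainly wrong because p between 0.008 and 0.05 means a 95% interval excluding zero.** An omnibus interaction with 2 degrees of freedom has no single interval, and a Bonferroni level can be described by its family-wise 95% confidence. The label is unclear, but this argument does not prove it wrong.

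A repeated-measures interaction with baseline as a level is also a valid test, though often less efficient. Finally, removing 0.008 takes away the only multiplicity adjustment in the article while several objectives are called primary. That objection stands, and the fix has to answer it.

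**Conclusion.** The point holds as a contradiction between Sample size estimation and Statistical analyses over both the test and the threshold, with nothing to say which governs the primary outcome. This part rests on the text alone and should be settled before unblinding.

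The 80% power with 67 per arm is confirmed only for an unadjusted comparison at 0.05. At 0.008 the same comparison drops by about 25 percentage points (80.4% to 55.8%). For the interaction at 0.008, power is 29% to 89% over assumed correlations of 0.3 to 0.7, and 45% to 62% at 0.5. The supported conclusion is that 80% is not established for that test. It is not that power must fall short, nor that the trial will be judged by that test.

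**What to change.** Name one primary test: the yoga minus control difference in EORTC QLQ-C30 cognitive functioning at end of chemotherapy, adjusted for its baseline value, at two-sided p<0.05 with a 95% confidence interval. Use ANCOVA, or the same contrast from a mixed model. This follows the significance rule and analysis already given in Sample size estimation. It also fits the time point that Assessment of cognitive functioning labels the primary endpoint, although that label is attached there to the neuropsychological battery.

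Remove the p≤0.008 rule for this outcome and report the after-cycle-3 contrast as secondary. State either that the neuropsychological battery and HRV objectives are secondary, or that they are tested with their own multiplicity control.

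The cost is rewording the Abstract's outcome statement, Sample size estimation and Statistical analyses so that they agree. The mid-chemotherapy contrast loses confirmatory status. No further patients or data are needed for this change.

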#### Monitoring

The progress of the study will be monitored by an internal project evaluation committee (IPEC) that meets periodically. IPEC will be responsible for trial data monitoring and quality assurance. The committee holds biannual meetings to ensure the trial’s proper conduct and safety and to offer/propose trial-related suggestions/modifications. In addition, the committee evaluates descriptive/interim reports that detail recruiting and enrolment numbers, sample characteristics, primary and secondary outcomes, and adverse events.

## Discussion

This study has planned to address the issues, extremely relevant in the area of breast cancer research and clinical management. There has been enhanced recognition of the potential of yoga as add on intervention for treatment induced adverse effects in breast cancer patients. This study will be the first of its kind to examine the efficacy of yoga on CRCI and CRCD in a controlled randomized control trial design.

Drugs that are a standard part of the chemotherapy regimen for breast cancer, such as Fluorouracil, Methotrexate, Paclitaxel and Taxanes, are recognized as neurotoxic and have a direct dose-response effect on cognition (57).

The yoga intervention module intended to use in this study has been shown to improve various aspects of cognitive and cardiac function with improved clinical outcomes in the non-cancer and cancer population (32, 39). Yoga has been shown to improve cognition in a variety of ways. First, yoga helps reduce stress and improve mood that affects cognitive functioning (36, 58). Secondly, yoga programs have been shown to improve attention span and the ability to shift attention and working memory on various neuropsychology tests (59). The attentional and alertness systems are critical components necessary for all aspects of cognition, including memory and language. Attention may be more amenable to change than other aspects of cognition (60, 61). Internalizing one’s awareness (attention) or mindfulness is an essential component of yoga that is known to help practitioners recognize stressful stimuli and modulate or slow down reactions to stressful stimuli, thereby helping them cope with stress. Studies have shown that yoga components such as asanas, pranayama, meditation, and relaxation improve attentional abilities in cognitive function (62). Third, both slow and fast breathing affect vagal afferents through their action on stretch receptors in the lung tissue and diaphragm and increase parasympathetic tone akin to relaxation response that calms down the mind (59). An earlier study on healthy volunteers saw a significant reduction in perceived stress and improvement in the following cognitive domains: attention, visuomotor speed and memory retention capacity in fast and slow pranayama groups (36). Fourth, asanas or postures facilitate physical training, strength, cardiorespiratory effort, aerobic capacity and balance, attentional faculties, and improved cognitive performance (63, 64). Studies have shown that cognitive spatial processing may rely on neural mechanisms that are also required to regulate posture; therefore, having balancing postures may help facilitate attention and spatial memory (62). Preliminary studies show the effects of a similar yoga program on cognitive functions in cancer patients (65, 66). A recent meta-analysis of yoga and cognition has shown benefits in improving cognitive function in adults and elderly populations showing substantial improvement in attention processing, memory, and executive functions as acute effects following yoga (67).

In current oncology practice, the ‘cardiovascular’ impact of cytotoxic therapies is estimated solely by changes in resting left ventricular ejection fraction (LVEF) which in turn is load-, rate-, and contractility-dependent and acute declines in myocardial function can be initially compensated to maintain cardiac output (68). Consequently, left ventricular dysfunction is a late marker, becoming evident after significant myocardial damage has already occurred resulted in need of alternative tools to identify patients in early stages who are at high risk for adverse cardiovascular impacts. Hence the current study used HRV along with echocardiography to detect CAD at a sub clinical stage. The study is the first to examine this neurocognitive changes correlating with CAD and serum cortisol. Another considerable strength of the trial is its multi-faceted assessment in understanding the impact of yoga intervention on brain structure (MRI) and functioning (BDNF) (fMRI), with neurocognitive functioning measures, cardiac vagal tone, and quality of life. Furthermore, these extensive outcome assessments on several levels involving various tools will allow researchers to investigate the relationship between subjective scales and objective indicators.

Hence, owing to the acute need for developing disease-modifying therapies that may improve and/or relieve symptoms associated with chemotherapy. The results from this study could have an immediate effect (yoga as an adjuvant treatment for breast cancer) as well as long term clinical implications in modulating cognitive function (development of novel yoga techniques based on understanding the mechanism of yoga). Moreover, the study also has important theoretical implications by shedding light on the role of yoga in modifying the behaviour of patients with Breast cancer receiving chemotherapy. In conclusion, this study will be the first to answer the leading edge questions in yoga and breast cancer research addressing CRCI and CRCD collectively.

